## Abstract

**Background:**

Early detection of scapholunate ligament (SLL) tears is essential after minor and major trauma to the wrist. The differentiation between stable and instable injuries determines therapeutic measures which aim to prevent osteoarthritis. Arthroscopy has since been the diagnostic gold standard in suspected SLL tears because non-invasive methods have failed to exclude instable injuries reliably. This prospective study aims to determine the diagnostic accuracy of dynamic, 4D computed tomography (CT) of the wrist for diagnosing instable SLL tears.

**Methods:**

Single center, prospective trial including 40 patients with suspected SLL tears scheduled for arthroscopy. Diagnostic accuracy of 4D CT will be tested against the reference standard arthroscopy. Radiologists will be blinded to the results of arthroscopy and hand surgeons to radiological reports. A historical cohort of 80 patients which was diagnosed using cineradiography before implementation of 4D CT at the study site will serve as a comparative group.

**Discussion:**

Static imaging lacks the ability to detect instable SLL tears after wrist trauma. Dynamic methods such as cineradiography and dynamic magnetic resonance imaging (MRI) are complex and require specific technical infrastructure in specialized centers. Modern super-fast dual source CT scanners are gaining popularity and are being installed gradually in hospitals and ambulances. These scanners enable dynamic imaging in a quick and simple manner. Establishment of dynamic 4D CT of the wrist in patients with suspected SLL tears in in- and outpatient settings could improve early detection rates. Reliable identification of instable injuries through 4D CT scans might reduce the number of unnecessary diagnostic arthroscopies in the future.

**Trial registration:**

This study was registered prospectively at the German Clinical Trials Register (DRKS) DRKS00021110. Universal Trial Number (WHO-UTN): U1111–1249-7884.

## Administrative information

Note: the numbers in curly brackets in this protocol refer to SPIRIT checklist item numbers. The order of the items has been modified to group similar items (see http://www.equator-network.org/reporting-guidelines/spirit-2013-statement-defining-standard-protocol-items-for-clinical-trials/).

## Introduction

### Background and rationale {6a}

Tears of the scapholunate ligament (SLL) are a common injury after wrist trauma [1]. Some partial ruptures of the ligament can be compensated, but undetected instable SLL tears usually lead to chronic wrist pain and disabling osteoarthritis [2]. The differentiation between stable and instable injuries influences therapeutic measures crucially. Stable SLL tears can be approached conservatively while complete or instable injuries should be repaired/stabilized [3]. Arthroscopy has long been the standard for any type of suspected SLL injury because results of diagnostic imaging are considered unreliable [4]. Thus, researchers have concentrated on developing methods to classify SLL tears noninvasively but dependably. In general, imaging of the SLL can be divided into static and dynamic techniques. Radiographs are the primary radiological method in cases of wrist pain but detect only static forms of SLL injuries accurately [5]. Through multi-slice CT and MRI of the carpal joints the SLL can be visualized directly. Direct arthrography improves accuracy of both methods from 56 to 100% [6, 7]. Early stages of SLL dissociation have been approached by dynamic methods such as cineradiography or cine MRI [5, 8]. Nevertheless, both arthrography and cineradiography are time-consuming; require specialized equipment, and personnel [9].

Evolution of CT technique towards dual source CT scanners as well as towards wider detectors paired with a higher number of detector rows offers another method for dynamic imaging paired with three-dimensional evaluations. Image quality of so called 4D CTs of the wrist has been described as excellent and inter-observer reliability for analysis of wrist kinematics seems promising [9–12]. Latest studies by Athlani et al. and de Roo et al. [13, 14] have investigated the SL gap with 4D CT in healthy and injured individuals. de Roo et al. presented a custom made device to standardize evaluation of the SL joint during radioulnar deviation [15]. Even though this approach improves the reproducibility of results, a custom made device will hardly be transferable to everyday routine. Both studies are lacking a diagnostic gold standard to compare the results of 4D CT. Nevertheless, 4D CT is described as feasible and its results helpful in differentiating SL instability.

Currently prospective data discussing the diagnostic accuracy of 4D CT of the wrist for classifying SLL tears is not available. Establishment of dynamic 4D CT of the wrist in patients with suspected SLL tears in in- and outpatient settings could improve early detection rates of this injury. Reliable identification of instable injuries through 4D CT scans might reduce the number of unnecessary diagnostic arthroscopies in the future.

### Objectives {7}

Primary objectives:
Analysis of diagnostic accuracy of 4D CT for the differentiation between stable and instable SLL tears preoperatively.Comparison of diagnostic accuracies of 4D CT and cineradiography.

*Secondary objectives:*
Can 4D CT scans of the wrist detect secondary injuries as opposed to radiography?How do the stages of scapholunate dissociation correlate with the time interval between diagnostics and trauma?Are measured effective radiation skin doses in-vivo and calculated skin doses during 4D CT similar?Which diagnostic algorithm can be proposed for suspected SLL tears?

### Trial design {8}

Prospective, exploratory study of diagnostic accuracy of 4D CT with arthroscopy as reference test adhering to the Standards for Reporting of Diagnostic Accuracy Studies (STARD) guidelines [15].

Additional comparison of sensitivity and specificity of 4D CT in detecting instable SLL tears to that of cineradiography observed in a historical cohort.

## Methods: participants, interventions and outcomes

### Study setting {9}

Single center study at an urban trauma hospital with a dedicated Department of Radiology specialized in musculoskeletal injuries and a Department of Hand-, Replantation- and Microsurgery located in Berlin, Germany.

### Eligibility criteria {10}

Eligible patients for prospective inclusion with suspected SLL tear are scheduled for diagnostic arthroscopy. 40 consecutive patients will be enrolled according to predefined criteria:
Inclusion criteria: patients > 18 years, written consent.Exclusion criteria: inability to consent, patients < 18 years, pregnancy, considerably limited range of radio-ulnar motion, incompliance to the rehearsed radio-ulnar motion, scapholunate advanced collapse (SLAC), previous carpal instability or carpal operation, incomplete historical records.
Patients with distal radius fractures and previous stabilization of the fracture will not be excluded per se. Only if these patients are not able to perform the required radio-ulnar motion due to pain or stiffness, they will be excluded. Patients with previous carpal instabilities or carpal operations i.e. due to scaphoid fractures will be excluded from this study as well.

A historical cohort consisting of 80 consecutive patients with the same inclusion and exclusion criteria who were diagnosed with cineradiography preoperatively during the pre-4D CT era will serve as comparison for the diagnostic value of the new method.

Two radiologists with more than 6 years of experience in musculoskeletal radiology will evaluate preoperative 4D CT scans and cineradiographies independently.

Arthroscopies will be performed by specialized hand and wrist surgeons.

### Who will take informed consent? {26a}

Written consent will be obtained by the attending hand surgeon or radiologist.

### Additional consent provisions for collection and use of participant data and biological specimens {26b}

Patients eligible for retrospective inclusion will be notified and informed about the study and asked for written consent via mail by the study center.

### Interventions

#### Explanation for the choice of comparators {6b}

The newly established imaging technique 4D CT has to be evaluated and tested for diagnostic accuracy. The diagnostic gold standard arthroscopy will serve as the reference test and prevent therapeutic gaps in case of inaccurate preoperative diagnosis.

For comparative results an additional evaluation of preoperative cineradiograms, the previous diagnostic/imaging standard of the study center, will be enclosed in a retrospective approach. Classifications of SLL injuries on cineradiograms will also be evaluated against the results of arthroscopy.

#### Intervention description {11a}

All patients with a typical trauma mechanism and wrist pain presenting through the ambulance or emergency room will be screened for eligibility. Patients will be examined and will receive radiographs of the wrist in two planes routinely. In cases of suspected SLL tear and indication for arthroscopy, patients will be informed about the possibility of study participation by the attending hand surgeon.

According to the inclusion and exclusion criteria 40 participants will be enrolled consecutively after written consent.

4D CT scans of the injured wrist will be performed preoperatively and analyzed by two specialized radiologists. Coronal reconstructions will be used to measure the maximum and minimum scapholunate distance (SLD). On sagittal reconstructions the scapholunate (SL) and radiolunate (RL) angle will be determined to classify SLL tears as stable or unstable.

The patients will not be exposed to radiation for research purposes. Arthroscopy will be performed as the diagnostic gold standard within the same week to classify the type of SLL tear according to the European Wrist Arthroscopy Society (EWAS) and Geissler [16, 17]. Primary reconstruction and temporary arthrodesis will be performed when necessary, but the surgical therapy will not be part of the study.

We will conduct an additional screening of historical patient records for eligibility, inclusion, and exclusion criteria. These historical patients with a typical trauma and wrist pain were also examined clinically and received radiographs of the wrist in two planes routinely. In cases of suspected SLL tear, cineradiography was performed before arthroscopy. After written consent 80 consecutive patient who were diagnosed through cineradiography before arthroscopy will be enrolled. Measurement of minimum and maximum SLD on anterior-posterior projections, of SL angle, and RL angle on lateral projections will be measured to classify SLL tears as stable or unstable and to compare these results to the findings of arthroscopy. The diagnostic accuracy of cineradiography will serve as a comparison for the sensitivity and specificity of 4D CT in suspected SLL tears.

#### Criteria for discontinuing or modifying allocated interventions {11b}

Eligible patients who are incapable of performing the radio-ulnar motion required for dynamic evaluation of the SLL will be excluded from the study. Patients who withdraw their consent for arthroscopy will be excluded from the study.

Patients will be able to withdraw their consent for participation at any time during the trial. Patients with incomplete historical records will be excluded from retrospective analysis.

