#### Strategies to improve adherence to interventions {11c}

Participants will be informed about the indication for arthroscopy irrespective of study participation. Close examination and clinical testing will reduce the number of patients who will have to be excluded due to an inability to perform the required radio-ulnar motion.

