### Data collection and management

#### Plans for assessment and collection of outcomes {18a}

Hand surgeons will be trained to examine patients during screening in a standardized fashion. Arthroscopies will be performed with the patient under general or regional anesthesia. At first, the membranous or proximal part of the SLL complex is visualized and the tear located through a 3/4 and 5 U portal. The SLL will be examined using a 2.4-mm arthroscope with a 30° wide angle lens (Storz, Erlangen, Germany) and probed with a hook. A tear will be differentiated into an avulsion from the lunate or scaphoid or a midsubstance ligament rupture. Secondly, through the midcarpal ulnar (MCU) and midcarpal radial (MCR) portals the SLL tear will be classified. Surgical reports will be descriptive, but they will include a final EWAS/Geissler classification to describe stability of the SL joint on a case report form (CRF) [16, 17]. The following data will be documented by hand surgeons on paper CRFs [Table 4].

**Table 4 Tab4:** Case Report Form

Patient-ID:		
**Screening:** Date		
Suspected SLL tear	Yes	No
Indication for arthroscopy	Yes	No
> 18 Years	Yes	No
Ability to perform radio-ulnar motion	Yes	No
Written informed consent	Yes	No
**Exclusion criteria:** Date		
Pregnancy	Yes	No
Incompliance for radio-ulnar motion		
SLAC	Yes	No
**Enrolment:** Date		
Date of enrolment		

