**Epidemiology:**		
Gender	Male	Female
Side of injury	Right	Left
Handedness	Right	Left
Date of injury		
Age at the day of injury		
**Clinical examination:** Date		
Watson-Test	Positive	Negative
Localized pain during compression of dorsal SLL	Yes	No
**Arthroscopy:** Date		
Age at the day of arthroscopy		
EWAS/Geissler Stadium		
Stability	Stable	Unstable

4D CTs will be acquired using a dual-source scanner with 2 × 192 rows and a detector width of 6 cm (Somatom Force, Siemens, Germany). Patients will be placed in prone position with the injured wrist reaching into the gantry (“superman position”). Patients will be instructed to perform a radio-ulnar movement during an 8 s scan cycle. Forearms will only be lightly fixated with a tape as a reminder for the patients to reside to wrist movements only. Postprocessing will be performed using a designated software (Syngo.Via Version VB10B-VB30A, Siemens, Germany). Reconstructions include dynamic 5 mm and 1 mm coronal reconstructions as well as static coronal and sagittal reconstructions of 2 mm. Table 5 summarizes the acquisition parameters of 4D CT.

**Table 5 Tab5:** Parameters of 4D CT

Tube voltage (kV)	80
Milliamperage (mAs)	70
Section thickness (mm)	1
Length (mm)	56
Number of slices	1254
Collimation	384 × 1 mm
Reconstruction matrix	Soft-tissue and bone kernel
Image reconstruction	512 × 512

Radiologists will document results of 4D CT in a standardized manner to describe stability of the SLL ([20], Table 6). SLD will be measured in the center of the SL joint during radio-ulnar motion at minimum and maximum width [21, 22]. Carpal angles will be measured on sagittal reconstructions according to the radial axis [23, 24].

**Table 6 Tab6:** Radiological Report

Patient-ID:		
**Parameter:** Date		
Modality	4D CT	Cineradiography
Date of imaging		
SLD_min_		
SLD_max_		
SL angle		
RL angle		
**Stability**	Stable	Unstable

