## Discussion

Studies of diagnostic accuracy have the potential to improve the standard of medical care. Well conducted studies which are reported adhering to standardized guidelines allow for a generalizability of the topic [15]. Observational studies have the advantage of answering certain scientific questions in a rather descriptive manner while excluding any harm induced by study specific interventions. The lack of direct comparisons through a strict randomization protocol is a disadvantage of this study type.

On these grounds it can be expected that this prospective observational study will result in reliable calculations of diagnostic parameters of 4D CT of the wrist in diagnosing instable SLL tears. The comparison with a historical cohort on the other hand, will always be a means to atone for missing randomization and prospective comparisons.

In order not to over-estimate the clinical relevance of 4D CT, it will be crucial to minimize drop-outs after conducting the index test. The study protocol requires that all patients will have to have an indication for the reference test arthroscopy first to be eligible as participants. The number and reasons for drop-outs and excluded patients will be described in detail in the study report.

It can be expected that a positive outcome of the study and an increasing availability of 4D CT could have a grave impact on out-patient care. Since approximately 5% of all wrist sprains have an associated injury of the SLL [27], a broad availability of reliable primary imaging might improve early detection rates, reduce the incidence of resulting osteoarthritis, and the number of unnecessary diagnostic arthroscopies in the future.

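### The motion exclusion has no time point, so a failed 4D CT in an enrolled patient can be removed as if the patient were ineligible

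*Protocol article*

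**What the plan says.** Inability to perform the radio-ulnar motion appears in four places.

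- **Eligibility criteria {10}** list as exclusions: "considerably limited range of radio-ulnar motion, incompliance to the rehearsed radio-ulnar motion".
- **Case report form (Table 4, under {18a})** has the item "Ability to perform radio-ulnar motion" in its screening block and incompliance with the motion in its exclusion block. Both stand above the enrolment block.
- **Criteria for discontinuing or modifying allocated interventions {11b}** state: "Eligible patients who are incapable of performing the radio-ulnar motion required for dynamic evaluation of the SLL will be excluded from the study". No time point is attached.
- **Strategies to improve adherence {11c}** say of the surgeons' prior check that it "will reduce the number of patients who will have to be excluded due to an inability to perform the required radio-ulnar motion".

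The motion that the index test needs takes place at the scan: "Patients will be instructed to perform a radio-ulnar movement during an 8 s scan cycle" ({18a}, after Table 4). Table 3 puts imaging after enrolment. Arthroscopy is indicated before a patient can join ({11a}, Discussion) and does not depend on the 4D CT result ({17b}). The Discussion promises to report drop-outs and exclusions with their number and reasons.

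**The concern.** A patient who cannot do the motion at screening lies outside the target population. A patient who passes screening, enrols and then cannot do it in the scanner has had an index test that gave no usable answer. The first limits to whom the results apply. The second is an outcome of the test under study.

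The rule in {11b} does not distinguish them. If it is applied at the scan, index-test failures leave the denominators of sensitivity and specificity, although their reference result will normally be available. The reported accuracy then applies to patients in whom the scan worked. The primary objective in {7} carries no such restriction, and the Discussion draws consequences for suspected tears in general, including fewer diagnostic arthroscopies. {10} names pain and stiffness as reasons for inability. These could be related to the injury itself, so the loss need not be random.

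**Working it through.** **Step 1: can the rule act after enrolment?**

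- For screening only: {10} is an eligibility list, Table 4 records the motion check before enrolment, and {11b} also repeats another eligibility rule (incomplete historical records).
- For later use: {11b} concerns discontinuation and speaks of patients who are already *eligible*. Its next sentence removes patients who withdraw consent for arthroscopy, which can happen after enrolment. {11c} expects testing to lower the number of exclusions, not to abolish them. The scan is done prone with the arm reaching into the gantry, so passing a clinical check does not guarantee success there.

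Both readings are open. The text permits removal at the scan but does not establish that it will occur.

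**Step 2: is there a figure in the plan to reproduce?** There is no failure rate, expected accuracy or precision target. The 40 patients come from feasibility: 30 arthroscopies a year × 2 years = 60, and 40/60 = 67%, which is coherent but says nothing about failed scans.

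**Step 3: possible size.** Let *f* be the share of enrolled patients without a usable scan. If failure is unrelated to accuracy,

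accuracy with failures counted as errors = accuracy in evaluable scans × (1 − *f*).

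| Accuracy in evaluable scans (assumed) | *f* = 0 | 5% | 10% | 20% |
|---|---|---|---|---|
| 90% | 90% | 85.5% | 81% | 72% |
| 80% | 80% | 76% | 72% | 64% |

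In whole patients, assume 20 of the 40 are unstable and sensitivity in evaluable scans is about 90% (exact 95% intervals in brackets):

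| Failed scans among the 20 unstable | Failures removed | Failures counted as missed | Difference |
|---|---|---|---|
| 0 | 18/20 = 90% (68–99) | 18/20 = 90% (68–99) | 0 |
| 1 | 17/19 = 89.5% (67–99) | 17/20 = 85% (62–97) | 4.5 points |
| 2 | 16/18 = 88.9% (65–99) | 16/20 = 80% (56–94) | 8.9 points |
| 4 | 14/16 = 87.5% (62–98) | 14/20 = 70% (46–88) | 17.5 points |

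Each failed scan in an unstable wrist therefore opens a gap of about 4 to 5 points. Specificity follows the same arithmetic in the stable group.

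The split matters. With two failures in all, one per group gives a sensitivity of 85% with failures counted as missed. Both in the unstable group gives 80% and leaves specificity untouched.

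**The case against.** A reader might infer that enrolled patients will be dropped and that 4D CT accuracy is therefore overstated. The documents do not support that. The rule says *eligible*, not *enrolled*. {10} and Table 4 place the check before enrolment, and if all failures are caught there the effect is nil.

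A reader might also take the Discussion as the protocol's own admission of this bias: "In order not to over-estimate the clinical relevance of 4D CT, it will be crucial to minimize drop-outs after conducting the index test". That sentence concerns losses after the index test has been carried out, and the safeguard that follows it is that arthroscopy must already be indicated. It addresses scanned patients who lack a reference result, not patients in whom the scan failed.

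Further points on the other side stand. Accuracy among patients able to perform the motion is a legitimate quantity if labelled as such. Counting every failure as an error is a worst-case convention: it makes a failed scan a false negative in an unstable wrist and a false positive in a stable one, which no single decision rule does. The historical cohort has the same exclusion criteria and also loses incomplete records, so penalising failures only for 4D CT would tilt the comparison against it. The study is declared exploratory, and fuller handling of unreadable scans may be in a document not shown.

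These points reduce the claim but do not remove it. The rule in {11b} is stated, not merely left out, and it can be followed in a way that deletes failures. The promised account of exclusions makes them visible without returning them to the estimates.

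**Conclusion.** The concern holds in a limited form. {10}, {11b}, {11c} and Table 4 do not separate ineligibility before enrolment from a non-diagnostic index test after it, and {11b} as worded lets the latter be removed. Sensitivity and specificity *can* then be overstated, provided that they are presented as performance in all patients with a suspected tear.

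The size cannot be derived from the protocol. It is zero if screening catches every failure. Under the assumptions of 20 unstable patients and about 90% sensitivity in evaluable scans, it is about 4 to 5 points of sensitivity per failed scan in an unstable wrist. The equal-failure formula further assumes that failure is unrelated to accuracy, which the protocol gives no means of checking.

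**What to change.** 1. Reconcile {10}, {11b}, {11c} and Table 4 so that the motion exclusion acts only before enrolment.
2. Keep every enrolled patient who undergoes arthroscopy. Classify a failed or unreadable 4D CT as non-diagnostic and show a 3×2 table: 4D CT unstable, stable or non-diagnostic against arthroscopy unstable or stable.
3. Report complete-case sensitivity and specificity, labelled as applying to patients with an evaluable scan, together with a pre-specified sensitivity analysis that counts non-diagnostic scans as errors.
4. Use the evaluable-scan figures for the comparison with cineradiography, unless historical failures can be identified and counted in the same way.
5. Report patients who were scanned but had no arthroscopy with their 4D CT class, as far as their consent allows.

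Settle this before the statistician joins the two departments' data, so that the denominator is not chosen with results in view. The cost is a change of wording, a little more analysis and possibly slightly less favourable figures. No extra procedure is needed.
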